### Data management

During the study, the investigators will regularly fill in the case report forms (CRF). Database management and quality control for the study will be performed by an independent statistician. Structured data elements from the CRFs will be entered into the database and reviewed using double data entry for verification. Information entered into the database will be systematically checked and evident errors will be corrected. All of the omissions and/or questions concerning the data will be discussed with the investigator in order to preserve the completeness of the database.

### Statistical analysis

Baseline demographic characteristic and clinical variables will be summarized for each arm of the study. Continuous data will be presented as arithmetic means and SD for normally distributed variables or as medians and inter-quartile ranges (25 to 75th) for abnormally distributed variables. Normality will be tested by the Shapiro-Wilk test.

Comparison of two groups will be based on parametric Student’s two-sample *t*-test, or Cochran-Cox test or non-parametric Mann–Whitney test as appropriate. Student’s paired *t*- or Wilcoxon’s test will be used to compare continuous variable differences between baseline and the end of observation period.

Categorical data will be given as absolute and relative frequencies (percentages). The differences in proportions between them will be examined using the chi-square - test with Yates’s correction or Fisher’s exact test as appropriate.

A logistic regression model will be used to identify independent predictors of response to therapy. For the longitudinal analysis, curves of cumulative probability of events will be constructed according to the Kaplan-Meier method, and the cumulative events rates will be compared by the log-rank test. A Cox proportional hazards regression analysis will be performed to assess for any potential influence of covariates. The assumptions of the Cox proportional hazards model will be checked by visual inspection of the log-log survival function by time curve.

Due to the possibility of the treatment crossovers, all major treatment comparisons between the randomized group in this trial will be performed according to both the intention-to-treat and the per protocol principles.

All null hypothesis will be two-tailed with a 0.05 type I error rate.

Statistical analysis will be performed using the SAS 9.2 statistical package (SAS Institute Inc., Cary, NC, USA).

The investigation conforms with the principles outlined in the Declaration of Helsinki [21]. The local ethics committee (that is the Ethics Committee of the Institute of Cardiology, Warsaw, Poland) has approved the study protocol including the written informed consent form (approval number: IK-NP-0021-47/1378/13).

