**Table 1 Tab1:** **The inclusion and the exclusion criteria for the Pilot-CRAfT study**

Inclusion criteria:	
1)	Permanent or long-standing persistent AF (definitions according to the latest ESC guidelines on AF)
2)	At least three months after the procedure of a CRT device implantation
3)	A CRT device with the presence of a right atrial electrode
4)	Age: ≥18 years old
5)	Effectively biventricular paced captured beats percentage <95%
6)	Effective therapy with oral anticoagulants for at least three weeks
7)	Written informed consent
Exclusion criteria:	
1)	Reversible causes of AF
2)	Significant valve disease
3)	Advanced AV block (including: AVJA)
4)	Contraindications to amiodarone (hyperthyroidism, non-compensated hypothyroidism, drug intolerance, QT >460 ms for men, QT >450 ms for women)
5)	Long-QT syndrome
6)	Cardiac transplantation in six months
7)	Life expectancy less than one year
8)	LA diameter larger than 6 cm
9)	Heart failure decompensation within 48 hours before the qualification
10)	Chronic dialysis
11)	History of alcohol abuse
12)	Pregnancy or lack of effective contraceptive therapy (in case of females in the reproductive age)
13)	Participation in other clinical trial

AF, atrial fibrillation; AV, atrioventricular; AVJA, atrioventricular junction ablation; CRT, cardiac resynchronization therapy; ESC, European Society of Cardiology; LA, left atrium.

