**Table 2 Tab2:** **Secondary endpoints of the Pilot-CRAfT trial**

	Secondary endpoints:
BiVp%:	
•	BiVp% change from baseline.
Physical competence:	
•	6MWT distance
•	Peak oxygen uptake (peak VO_2_) in CPX
•	NYHA functional class
The echocardiographic assessment of the reverse remodelling:	
•	Increase in left ventricle ejection fraction (LVEF)
•	Decrease in left ventricle diastolic diameter and volume (LVEDD, LVEDV)
•	Decrease in left ventricle systolic diameter and volume (LVESD, LVESV),
•	Decrease in size of the left atrium (LA)
•	Decrease of the severity of mitral insufficiency
Quality of life:	
•	Measured with the Minnesota Living with Heart Failure Questionnaire
Clinical endpoints:	
•	Unplanned hospitalizations due to heart failure exacerbations
•	Death
•	Cardiovascular death
•	Hospitalizations due to cardiovascular causes
•	Stroke/TIA
•	A combined endpoint including unplanned hospitalizations due to cardiovascular causes or death
Heart arrhythmias:	
•	AF - using *mode switch* to measure time of AF with fast ventricular rate
•	Ventricular tachycardia including *torsade de pointes* tachycardia and ventricular fibrillation
In the CRT-D subgroup:	
•	Number of adequate and inadequate shocks (separately)
•	The prevalence of electrical storm
Adverse events:	
•	Pharmacotherapy related
•	Device related
•	Cardioversion related
•	AVJA related

The clinical endpoints, the occurrence of heart arrhythmias and adverse events are collected for safety measures. All of the endpoints will be assessed at three-months and one-year from the baseline timeframes.

6MWT, six-minute walk test; AF, atrial fibrillation; AVJA, atrioventricular junction ablation; BiVp%, effectively biventricular paced captured beats percentage; CPX, cardiopulmonary exercise test; CRT-D, cardiac resynchronization therapy with defibrillator function; TIA, transient ischemic attack.

Based on the results of the primary endpoint, the authors plan to perform a preliminary identification of the factors predicting the response to the *rhythm control* strategy.

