## Statistical methods

### Sample size

The calculation of a sample size was made based on the estimated results in the groups for the primary endpoint (BiVp%) and the following assumptions: 1) the mean difference of BiVp% between groups would be 8% and standard deviation (SD): 15%; 2) probability of a type I error: 0.05; 3) probability of a type II error: 20%; 4) the type of test: Student’s two-sample *t*-test; 5) drop-out rate: 8%.

A power analysis revealed that a minimum of 30 patients per group will be required to assure at least 80% power for detecting the anticipated between-group differences in BiVp% and to compensate for the expected drop-out rate.

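### No single primary test is fixed and baseline BiVp% goes unused: the test the data are likely to select does not estimate the 8-point mean difference the trial was sized on

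*Protocol article*

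**What the plan says.** The Sample size section assumes "the mean difference of BiVp% between groups would be 8% and standard deviation (SD): 15" percent, with "probability of a type I error: 0.05", 80% power and Student's two-sample t-test. The Endpoints section defines the primary endpoint as mean BiVp% over the whole 12-month follow-up.

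The Statistical analysis section sets out the methods for continuous variables:

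- After the descriptive statistics: "Normality will be tested by the Shapiro-Wilk test".
- Between arms: "Comparison of two groups will be based on parametric" Student's t-test, or Cochran-Cox, or Mann-Whitney, with the choice left to suitability.
- Within arms: a paired t-test or Wilcoxon's test "will be used to compare continuous variable differences between baseline and the end of observation period".
- Error rate: "All null hypothesis will be two-tailed with a 0.05 type I error rate".

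The primary endpoint has no rule of its own. Covariates appear only in the logistic model for predictors of response and in the Cox model.

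Baseline BiVp% must be available for everyone. Table 1 requires "Effectively biventricular paced captured beats percentage <95" percent for entry, and Table 2 lists "BiVp% change from baseline" as a secondary endpoint. The Follow-up section also schedules baseline 6MWT, echocardiography, CPX and MLHFQ.

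**The concern.** The section used to size the trial and the section used to analyse it do not describe the same analysis. The first commits to a difference in means by a t-test. The second lets the observed distribution decide whether the reported result concerns means or ranks. For a percentage capped at 100 in an AF population, skewness is the likely case, so the test used for sizing may seldom be the one reported.

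Two things are at stake. The first is interpretation. The Discussion expects only some rhythm-control patients to keep sinus rhythm, and AVJA is optional in the control arm, so the arms may well differ in spread and shape. A significant rank test could then arise without any difference in mean BiVp%. The second is precision. With 60 patients, chance imbalance in baseline BiVp% and unexplained variance are both substantial, and the variable that would reduce them is already collected.

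The paired tests raise a smaller issue. They do not compare the two strategies. Because patients enter on a low BiVp%, some within-arm improvement is expected without any treatment effect.

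**Working it through.** **Inputs from the protocol.** Difference 8, SD 15, two-sided alpha 0.05, power 80%, drop-out 8%, 30 per arm. Patients analysed per arm: 30 × 0.92 = 27.6, taken as 28.

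**The plan's own figure.** n per arm = 2 × (15/8)² × (1.96 + 0.84)² = 55.2, so 56; 56/0.92 = 60.9, so 61. The stated 30 is not reproduced. Dropping the factor 2 gives 27.6, and 27.6/0.92 = 30.0. That is a separate error, but it explains why unadjusted power starts near 50%.

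**Cost of leaving out baseline, like for like.** The comparison is a mean-based test with and without baseline as covariate. Residual SD = 15 × √(1 − r²), where r is the correlation of baseline with follow-up BiVp%. Noncentrality = (8/residual SD) × √(28/2). The protocol gives no r, so a range is assumed.

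| r | Residual SD | Noncentrality | Power, 28 per arm |
|---|---|---|---|
| 0 (unadjusted) | 15.00 | 2.00 | 50% |
| 0.3 | 14.31 | 2.09 | 54% |
| 0.5 | 12.99 | 2.30 | 62% |
| 0.6 | 12.00 | 2.49 | 69% |
| 0.7 | 10.71 | 2.79 | 78% |

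An unadjusted change score has SD 15 × √(2(1 − r)) if baseline SD is also 15. At 27.6 per arm its power is 38%, 49% and 71% for r = 0.3, 0.5 and 0.7. ANCOVA at the same size gives 53%, 61% and 78%.

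**Which test would be reported.** Simulation with 28 per arm. Assumptions: Mann-Whitney is used if Shapiro-Wilk rejects at 5% in either arm; otherwise Levene's test decides between Student and Welch. Skewed data are drawn from beta distributions on 0 to 100.

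- Normal data: Mann-Whitney is used in 10% of trials, type I error is 4.9%, and power is 51%, the same as the t-test. Here the rule is harmless.
- Skewed, SD 15, means 75/83, 80/88 and 84/92: Shapiro-Wilk rejects in 92% to 100% of trials. Power is 50% to 53% for the t-test and 61% to 94% for Mann-Whitney.
- Skewed, both means 85, SDs 20 and 10: Mann-Whitney rejects in 39% to 41% of trials across runs, the t-test in about 6%, and ANCOVA in 6%.
- Skewed, both means 85, SDs 18 and 12: 19% against 5%.

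In the last two settings Mann-Whitney is correctly detecting different distributions. The difficulty is that its rejection cannot be read as a difference in mean BiVp%.

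**Within-arm change.** Assumed true mean 85 to 90, between-patient SD 8 to 12, within-patient SD 5 to 8, entry only if the baseline reading is below 95. With no treatment effect, the mean gain is 0.7 to 3.1 points across the corners of these ranges. They imply a follow-up SD of about 8 to 13, below the planned 15, so this shows direction and rough order only.

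**The case against.** An unadjusted two-sample test in a randomised pilot is valid. The article condenses a longer protocol, and covariate adjustment is often left to an analysis plan. That Shapiro-Wilk drives the choice of test is inferred: its sentence belongs to the descriptive statistics, and the link is only the natural reading. These points stand, but they do not dispose of the matter. The section does not stay silent. It names a menu, and that menu does not match the test used for sizing.

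Three stronger readings are tempting and are not supported:

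- *That the plan as a whole wastes power.* On skewed data Mann-Whitney, the test likely to be chosen, reached 61% to 94% power where mean-based ANCOVA reached 53% to 67%. The loss exists only when mean-based tests with and without baseline are compared, and it may be small: 50% to 54% at r = 0.3. A low r is plausible, because entry is cut off at 95% and because restored sinus rhythm or AVJA may detach follow-up from baseline.
- *That change in BiVp% is tested only by paired tests.* The section lists paired tests beside the between-arm tests, and the change endpoint can be compared between arms. A change score also uses baseline, by subtraction. Regression to the mean affects both randomised arms and cancels in expectation between them.
- *That ANCOVA rescues 30 per arm.* After drop-out it reaches 80% power only if r is slightly above 0.7.

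**Conclusion.** The point holds in a limited form. The protocol sizes on a mean difference by Student's t-test but leaves the primary test to be chosen from the data, and it ignores a baseline value held for every patient. The likely consequence is a rank test that does not estimate the planned 8 points and that can reject in about 40% of trials when means are equal but spreads differ strongly. That figure depends on the assumed beta shape and SDs of 20 and 10; it falls to 19% at 18 and 12. The gain from baseline adjustment, 4 to 28 percentage points of power over r = 0.3 to 0.7, depends on an undocumented correlation. The within-arm tests are a lesser matter: they are no evidence about the strategies, and their bias depends on assumed variances.

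The inconsistency between the sizing and analysis sections is certain from the text; the sizes are illustrative. It should be corrected before the analysis. The shortfall in sample size (about 56 per group before drop-out, not 30) is a separate and larger problem.

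**What to change.** In the Statistical analysis section, replace the menu for the primary endpoint with one analysis: a linear model (ANCOVA) of 12-month mean BiVp% on arm and baseline BiVp%, with no normality pre-test. Report the adjusted mean difference with a 95% confidence interval, and prespecify robust, bootstrap or permutation inference to deal with skewness. Add one rank-based sensitivity analysis.

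Use the same baseline-adjusted between-arm model for the BiVp% change endpoint and for LVEF, LV and LA size, peak VO2, 6MWT and MLHFQ. Report within-arm changes descriptively and drop the paired tests as evidence of effect.

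The cost is a change of wording and a few lines of SAS; no new data or patients are needed, and recruitment is still open according to the Trial status section. The downside is that on strongly skewed data the mean-based analysis may have less power than Mann-Whitney. The rank-based sensitivity analysis would show this.

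### The planned Kaplan-Meier curves name no events and make no provision for competing deaths, so if used for hospitalization, stroke/TIA or cardiovascular death they would slightly overstate 12-month risk

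*Protocol article*

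**What the plan says.** The Statistical analysis section of the protocol article gives one method for event probabilities over time and one way of comparing them: "curves of cumulative probability of events will be constructed according to the Kaplan-Meier method, and the cumulative events rates will be compared by the log-rank" procedure. On covariates it adds: "A Cox proportional hazards regression analysis will be performed to assess for any potential influence of covariates". The events are not named. No cumulative incidence function or other competing-risk method is mentioned.

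Table 2 lists six clinical endpoints. Four of them can be prevented by a death that is not itself the event: "Unplanned hospitalizations due to heart failure exacerbations", "Hospitalizations due to cardiovascular causes", stroke/TIA and "Cardiovascular death". The other two, all-cause death and the composite of unplanned cardiovascular hospitalization or death, count every death as an event. The note to the table gives their purpose: "The clinical endpoints, the occurrence of heart arrhythmias and adverse events are collected for safety measures".

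The Statistical analysis section also provides for categorical data to be reported as counts and percentages.

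**The concern.** A patient who dies without having been hospitalized can no longer be hospitalized. Kaplan-Meier applied to hospitalization alone has to censor that patient. Censoring assumes that the patient would later have had the event at the rate seen in those still under observation. One minus Kaplan-Meier then estimates the risk in a hypothetical population in which nobody dies first, which is higher than the risk in the patients studied. The same holds for stroke/TIA. For cardiovascular death, only non-cardiovascular death competes.

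The stake is the absolute 12-month risk read off the curves. These endpoints are collected for safety, where absolute risk matters. The aim of the study also includes collecting data to design a larger trial on mortality and morbidity, and a hospitalization rate taken from such a curve would be somewhat too high as a planning value.

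**Working it through.** **No figure to reproduce.** The article gives no death, hospitalization or stroke rate, so every rate below is an assumption. From the article come the 12-month follow-up (Follow-up section) and the 30 patients per group (Sample size section).

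**Direction.** Let *d* be the events and *Y* the number at risk at each event time.
- One minus Kaplan-Meier adds up S_KM × *d*/*Y*, where S_KM is the event-free curve with deaths censored.
- Aalen-Johansen cumulative incidence adds up S_all × *d*/*Y*, where S_all is the probability of being both alive and event-free.
- S_all falls below S_KM after the first competing death, so every later event counts for more under Kaplan-Meier. The direction needs no assumption about the shape of the hazards.

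**Size.** Assume constant, independent hazards over 12 months. Let h be the event risk that Kaplan-Meier would show and m the 12-month risk of the competing death.
- a = −ln(1 − h) and b = −ln(1 − m)
- One minus Kaplan-Meier = h
- Cumulative incidence = a/(a + b) × (1 − exp(−(a + b)))

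Worked example, h = 0.30 and m = 0.10: a = 0.3567, b = 0.1054, a + b = 0.4620. Then 1 − exp(−0.4620) = 0.370 and a/(a + b) = 0.772, so cumulative incidence = 0.772 × 0.370 = 0.286. The excess is 30.0 − 28.6 = 1.4 points.

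| Competing mortality | Kaplan-Meier risk | Cumulative incidence | Excess (points) | Patients per 30 |
|---|---|---|---|---|
| 5% | 30% | 29.3% | 0.7 | 0.2 |
| 10% | 30% | 28.6% | 1.4 | 0.4 |
| 15% | 30% | 27.8% | 2.2 | 0.7 |
| 20% | 30% | 27.1% | 2.9 | 0.9 |
| 20% | 40% | 36.2% | 3.8 | 1.1 |
| 5% | 3% | 2.92% | 0.1 | 0.02 |
| 20% | 5% | 4.49% | 0.5 | 0.15 |

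The last two rows stand for a rare event such as stroke. For a 30% event risk the relative excess is about 2.4% at 5% mortality, 5% at 10% and 11% at 20%.

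**Against sampling error.** A simulation of 20,000 arms of 30 patients with h = 0.30 and m = 0.10 gave mean values of 30.0% (Kaplan-Meier) and 28.6% (cumulative incidence). The standard error of the Kaplan-Meier estimate was 8.6 points, about six times the excess (8.6/1.4 = 6.1).

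**The case against.** The strongest objection is that the article does not assign Kaplan-Meier to these four endpoints. It speaks only of events, and Table 2 contains two endpoints for which the method is right. A condensed article may leave the assignment to a full protocol or analysis plan that is not shown. This stands in part: a reader might infer that all four endpoints are committed to Kaplan-Meier, and the text does not support that. It does name Kaplan-Meier, without restriction, as its only estimator of cumulative event probability, so following it for these endpoints would produce the excess.

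Three other limits also stand.
- A reader might infer that the planned tests are invalid. They are not: with competing deaths censored, log-rank and Cox compare cause-specific hazards, which is a legitimate question. Only the plotted absolute risks are affected.
- A reader might infer that the method keeps dead patients in the risk set. It removes them; the excess comes from assuming that they would have gone on to have events at the survivors' rate.
- A reader might infer that the later trial will be undersized. That does not follow, because counts and percentages are also planned and the composite includes death. With complete 12-month follow-up, the crude proportion equals the Aalen-Johansen estimate; with the assumed 8% drop-out it is only approximate.

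The figures may also be too high. Only deaths without a prior event compete, so if mortality rises after a heart failure admission, the 12-month mortality overstates the competing hazard. Table 1 excludes patients with a life expectancy under one year, which puts the 20% scenario at the upper end. For cardiovascular death the relevant rate is non-cardiovascular mortality alone.

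**Conclusion.** The point holds as a minor correction, conditional on Kaplan-Meier being used for any of the four endpoints that another death can prevent. In that case the 12-month absolute risk is overstated whenever events follow competing deaths. At assumed mortality of 5% to 10% and a 30% event risk, the excess is 0.7 to 1.4 points, less than half a patient per arm of 30. For a rare event it is about 0.5 points at most over the range shown. These sizes rest on constant, independent hazards and on rates that the article does not give.

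The excess is well inside the sampling error of this pilot, but it is systematic and more patients would not remove it. The primary endpoint, mean BiVp% over follow-up, is not touched. The Discussion already says that differences in the clinical endpoints will be hard to show, so no main conclusion depends on this.

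**What to change.** Amend the Statistical analysis section as follows:

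- Name the events. Keep Kaplan-Meier for all-cause death and for the composite.
- For heart failure hospitalization, cardiovascular hospitalization and stroke/TIA, report Aalen-Johansen cumulative incidence with death as the competing event. For cardiovascular death, use non-cardiovascular death as the competing event.
- Keep log-rank and Cox for these four endpoints, labelled as comparisons of cause-specific hazards.
- When planning the larger trial, use the cumulative incidence figures, or the crude 12-month proportions if follow-up is complete.

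The cost is a sentence or two of text and a little more analysis work. The data are the same, provided that dates and causes of death are recorded. The reported rates will be slightly lower.

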## Discussion

Based on the current knowledge, the authors assume that the *rhythm control* strategy would be at least as good as the *rate control* strategy in terms of BiVp%. The achievement of SR and satisfactory BiVp% in the *rhythm control* group may strengthen the underestimated position of cardioversion in the group of HF patients on CRT with concomitant permanent AF.

It may seem disputable whether the CRT patients with permanent AF will resume and maintain SR. As has been already mentioned, HF and AF are diseases that can negatively influence each other. In at least some of the patients, an occurrence of AF seems to be a marker of HF severity. We hypothesize that restoration of sinus rhythm, which would enhance the performance of CRT and enable better treatment of HF, may have beneficial effect on AF progression. Based on the evidence of the SR resumption phenomenon [13] and the study by Turco *et al*., this is highly probable. In the latter work it has been proven that - by means of a single cardioversion - SR is resumed in 82% of the patients and maintained for a 1 year in about 60% of the former AF-CRT patients [14]. We assume that the possibility of additional cardioversions and standard use of the amiodarone will elevate this percentage. Additionally, the results of the PVI isolation from the PABA-CHF trial in HF patients with AF are also appealing bearing in mind the initial differences between the populations of the PABA-CHF and our study (that is the lack of CRT in the PVI subgroup and paroxysmal character of the AF in half of the patients). After a 6-month observation period, 88% and 71% of patients who underwent PVI were free from AF depending on whether they received or did not receive antiarrhythmic agents [18].

The authors are fully aware that during the progression of HF, irreversible fibrous changes within the atria occur which promote AF and its maintenance [22], so it is unlikely that the proposed treatment strategy would be effective in all of the patients included. Hence, it seems crucial not only to establish the efficacy of proposed treatment strategy of rhythm control but also to define the subgroup of patients who would benefit the most from this strategy. An attempt to perform preliminary analysis of the non-responders as well as the ultra-responders would be made in the trial.

The standard use of amiodarone in both of the groups may seem disputable in the potential complications of this treatment and limited evidence of its efficacy. However, following the literature the use of amiodarone should facilitate sinus rhythm maintenance in the rhythm control group [1, 23, 24]. The use of the drug in the *rate control* group arises from its beneficial effect on AV node in this group of patients [1]. Moreover, it makes two of the treating arms more consistent. Following the latest ESC guidelines on management of AF [1], amiodarone is commonly used in patients with AF and depressed left ventricle ejection fraction and its potential adverse events, occurring in up to about 10% of patients according to the latest RCT comparing amiodarone with dronedarone [24], will be carefully monitored, including regular TSH measurements, QT evaluation and occurrence of arrhythmias at baseline visits and during the follow-up period.

One of the limitations of the trial is the number of the participants which surely has an impact on the statistical strength of the study. It would enable the researchers to assess the efficacy of the two treatment strategies on the primary endpoint only. The statistical difference within the clinical secondary endpoints of this study will be difficult to achieve. However, the lack of sufficient data about the CRT in the patients with concomitant AF necessitates the undertaking of an initial pilot study upon this issue.

The incoming results of the Pilot-CRAfT would enable the authors to prepare a parallel larger, well-designed multi-center study assessing the influence of both treatment strategies on ‘harder’ clinical endpoints, such as mortality and morbidity, as well as further analysis of the factors determining the response to the rhythm control strategy. The assessment of the efficacy of the rhythm control strategy in CRT and AF patients and the identification of the subgroup of patients who benefit from it the most would create an alternative to the currently recommended rate control strategy which has some considerable limitations.

Whatever the results of the trial, performing a prospective, randomized study on CRT patients with concomitant persistent forms of AF would finally provide strong scientific evidence data about the efficacy of CRT in this specific subgroup of patients. This urgently needed data has been long awaited.

